## 6.2 Patients with Bipolar Mania

Inclusion criteria: ① meeting the diagnostic criteria by the fifth edition of the Diagnostic and Statistical Manual of Mental Disorders (DSM-5) and currently during a manic episode; ② inpatients in Shanghai Mental Health Center; ③ clinical indications of receiving convulsive treatment, such as severe psychomotor excitement or retardation, attempts of suicide, being highly aggressive, pharmacotherapy intolerance, and ineffectiveness of antipsychotics; ④ age between 18 and 55 years old; ⑤ moderate to severe manic symptoms with scores of Young Manic Rating Scale (YMRS)  $\geq 10$ ; ⑥ Written informed consent.

Exclusion criteria: ① comorbidity with other mental disorders by DSM-5; ② with unremovable metal implants; ③ a laboratory abnormality with an impact on the efficacy of treatments or safety; ④ severe physical diseases (stroke, heart failure, liver failure, neoplasm, or immune deficiency), a laboratory abnormality with an impact on the efficacy of treatments or safety; ⑤ Alcohol or substance dependence in the 30 days prior to the start of the trial or in the 6 months prior to the trial; ⑥ failure to respond to an adequate trial of ECT; ⑦ being or intending to get pregnant during the study; ⑧ other conditions that investigators consider to be inappropriate to participate in this trial.

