## **9. Outcome Measures**

### **9.1 Primary outcomes**

Designated qualified psychiatrists assessed all patients' symptoms before and after the entire MST and ECT treatments. Manic symptoms were assessed by YMRS. The reduction rate of YMRS total scores was used as the primary outcome. The response is defined as a  $>50\%$  reduction of YMRS total scores compared to the baseline.

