### 360 **14.2 Statistical Analysis Plan**

361 We will use SPSS for statistical analysis, employing statistical methods such as t-  
362 tests, analysis of variance, and correlation analysis based on the data types and  
363 distribution characteristics. For the MRS data, LC-Model will be utilized. After  
364 preprocessing, resting-state fMRI data will be analyzed using software packages such  
365 as REST and GIFT.

366 (1) Baseline comparisons: To compare the differences in neurocognitive function,  
367 CI indicators, and resting-state fMRI measures between the MST group, ECT group  
368 and healthy control group; To explore the correlation between CI indicators and GABA  
369 levels detected within each group.

370 (2) Longitudinal comparisons: Compare the longitudinal changes of clinical,  
371 neurocognitive and CI measures before and after ECT and MST interventions.

372 (3) fMRI: the medial prefrontal cortex within the default mode network (DMN)  
373 will be chosen as a seed to calculate its functional connectivities the posterior cingulate  
374 gyrus, precuneus and the bilateral inferior parietal lobules. We hypothesize that patients  
375 with bipolar mania may show enhanced connectivity within the DMN, and this  
376 connectivity will be improved after MST or ECT intervention.

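### Section 14.2 names no MST-versus-ECT efficacy contrast and no baseline adjustment, so its before/after wording permits within-arm inference

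*Protocol*

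**What the plan says.** Section 4.4 gives the aim as a randomised comparison of the efficacy of MST and ECT, with the hypothesis that efficacy is comparable and that MST has fewer side effects.

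Section 9.1 fixes the endpoint: "The reduction rate of YMRS total scores was used as the primary outcome". Symptoms are rated "before and after the entire MST and ECT treatments", so each patient contributes one baseline and one post-treatment value. Response is a fall of more than 50% from baseline. Section 6.2 admits patients with a YMRS of 10 or more.

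Section 14.2 opens with "We will use SPSS for statistical analysis, employing statistical methods such as t", which runs over the line into "tests, analysis of variance, and correlation analysis based on the data types and" their distribution. Item (1) begins "1) Baseline comparisons: To compare the differences in neurocognitive function" and compares MST, ECT and healthy controls; it lists no clinical measure. Item (2), the only item that covers clinical outcomes, compares longitudinal change in clinical, "neurocognitive and CI measures before and after ECT and MST interventions". (CI in that quote means cortical inhibition.) Item (3) expects connectivity to improve after either treatment, again in before/after form.

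**The concern.** The comparison that the trial exists to make is not stated in the section that sets out its analysis. When 14.2 means a comparison of groups, in item (1), it names the groups and puts the word between in front of them. Item (2) does not. Two analysts could follow it faithfully and do different things: one compares change between arms, the other tests change within each arm.

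The second route is not protected by randomisation. There is no untreated patient arm, healthy controls are assessed only at baseline (Section 6.1), and MST is described as adjunctive (Sections 4.2 and 7). Change within an arm therefore mixes treatment with natural recovery, concurrent drugs and, on RBANS, practice. Given the hypothesis, two conclusions are tempting: that both arms improved and so are comparable, or that only one arm declined on cognition and so MST is safer. Neither is evidence on relative effect.

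The endpoint's scale adds a second reason to bring in baseline. A percentage reduction has the baseline score as its denominator, and that can be as low as 10. Baseline YMRS is collected in any case, yet no use of it as a covariate is stated.

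**Working it through.** **1. The plan's own figure.** Section 7 gives 30 per arm from n = 2π(1−π)[(u₁₋α + u₁₋β)/δ]², with α = 0.05 and a printed β of 0.80, read here as power 0.80. It cannot be reproduced, because π and δ are not given. Solved for δ at n = 30 and one-sided α (sum of u = 2.486), π = 0.7 gives δ = √(0.42 × 2.486² / 30) = 0.29; π = 0.8 gives 0.26 and π = 0.9 gives 0.19. Two-sided, the values are 0.33, 0.29 and 0.22. The formula is for a binary rate. The protocol therefore gives no planned power for the percentage reduction against which a loss could be measured.

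**2. Within-arm testing.** Suppose both arms are equally effective, are tested separately, and each test has power p. The chance that exactly one is significant is 2p(1−p): 50% at p = 0.5, 32% at 0.8, 18% at 0.9 and 2% at 0.99. For YMRS, within-arm power is probably high, so the likelier error is to read two significant falls as equivalence. For RBANS, the one-arm-only pattern is the greater risk.

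**3. Scale.** One YMRS point is 1/10 = 10% for a patient entering at 10 and 1/40 = 2.5% for one entering at 40.

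**4. ANCOVA against raw change scores.** Assume equal pre and post SD σ and pre-post correlation ρ. The variance of change is 2σ²(1−ρ) and the ANCOVA variance is σ²(1−ρ²), so the ratio is (1+ρ)/2.

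| ρ | Ratio | Variance saved | ANCOVA n per arm equal to 30 on change |
|---|---|---|---|
| 0.2 | 0.60 | 40% | 18 |
| 0.3 | 0.65 | 35% | 19.5 |
| 0.5 | 0.75 | 25% | 22.5 |
| 0.7 | 0.85 | 15% | 25.5 |

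**5. Against the stated endpoint, percentage reduction.** The documents give no YMRS mean, SD, correlation or effect, so all of these are assumed. Simulation: 30 per arm, 3,000 runs, two-sided 5%, baseline mean 28 (10 or above), post-treatment mean 10 and SD 7, arm difference 5 points. In the proportional rows, the post score and the effect scale with baseline. Power in %:

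| Baseline SD | ρ | t-test on % reduction | ANCOVA on post score | % reduction with baseline covariate |
|---|---|---|---|---|
| 5 | 0 | 71.0 | 76.1 | 74.6 |
| 5 | 0.2 | 76.4 | 77.9 | 76.2 |
| 5 | 0.3 | 80.0 | 80.5 | 79.2 |
| 5 | 0.5 | 86.1 | 87.7 | 86.7 |
| 5 | 0.7 | 91.7 | 96.9 | 96.5 |
| 5 | proportional | 76.2 | 74.0 | 75.2 |
| 8 | 0 | 62.2 | 76.9 | 70.7 |
| 8 | 0.2 | 69.1 | 78.3 | 74.2 |
| 8 | 0.3 | 76.2 | 81.2 | 77.5 |
| 8 | 0.5 | 86.2 | 88.8 | 85.7 |
| 8 | 0.7 | 94.0 | 96.3 | 94.5 |
| 8 | proportional | 75.9 | 73.3 | 75.5 |

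A second set assumed post-treatment mean 8, SD 6 and a difference of 4. With baseline SD 9, the t-test on percentage reduction against post-score ANCOVA gave 53% v 69% at ρ = 0, 79% v 82% at ρ = 0.5, and 71% v 66% in the proportional case. With SD 6 and ρ = 0.3 it gave 73% v 74%.

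So post-score ANCOVA ranges from about 5 points worse (71 − 66) to about 16 better (69 − 53). Adding the covariate to the reduction rate ranges from 1 point worse (76.2 − 75.2) to about 9 better (70.7 − 62.2 = 8.5 in the table). Rejection under the null was about 4 to 6% for all three methods.

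**The case against.** The strongest reply is that the protocol never calls the analysis unadjusted. The method list is introduced as examples and excludes neither ANCOVA nor a group-by-time analysis. Item (2) can be read as comparing change between ECT and MST, and the aim in Section 4.4 favours that reading. Model form and covariates are often left to a separate SAP, which may exist and is not shown. All of this stands. A reader might infer that 14.2 fixes an unadjusted or within-arm efficacy analysis; the text does not support that.

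It does not remove the point. Section 14.2 carries the title of an analysis plan, and it does describe the comparisons to be made. It names groups where it intends a group comparison and does not do so for efficacy. The direction of the primary comparison is more basic than a covariate list.

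A second reply is that the t-test on percentage reduction is valid, with type I error near 5%, is tied to the response definition, and is not always less powerful. This also stands: the ranking against post-score ANCOVA reverses when outcome scales with baseline, and the largest gaps need zero pre-post correlation. Nor is it shown that low-baseline patients dominate the variance. Under a baseline of mean 28 and SD 9 cut at 10, only about 5% enter below 15. The lack of follow-up in healthy controls is no defect in the MST–ECT contrast; it matters only if within-arm change is offered as an effect.

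**Conclusion.** The point holds as one of clarity and modest efficiency. Section 14.2 states neither the MST-versus-ECT efficacy contrast that Section 4.4 calls for nor any baseline adjustment, and its before/after wording leaves room for within-arm claims.

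A reader might go further and say that the plan wastes power. That is not established for the stated endpoint. The gain from post-score ANCOVA over an unadjusted t-test on percentage reduction lies between about nil and 16 points when the arm difference is constant across baselines, and turns into a loss of up to about 5 when the post score is proportional to baseline. Keeping the reduction rate and adding baseline YMRS is the safer choice: at most about 1 point lost and up to about 9 gained in the settings tried. The gain is clearer only against raw change scores, at 15–40% of the variance for correlations from 0.7 to 0.2, assuming equal SDs. All of these figures rest on assumed means, SDs, correlations and effects, since the protocol gives none.

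**What to change.** In Section 14.2, or in the SAP if there is one:

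- State the primary analysis as the MST minus ECT difference with a confidence interval, from a model with arm and baseline YMRS. The outcome may be end-of-treatment YMRS (ANCOVA) or the reduction rate with baseline YMRS as covariate. The second keeps the endpoint of Section 9.1 unchanged. Choose one before the data are seen.
- Use the same baseline-adjusted between-arm model for MADRS, RBANS and the cortical-inhibition measures.
- Label before/after change within an arm as descriptive, not as an effect of MST or of ECT.

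The cost is wording. Baseline values are already collected, no extra patients or visits are needed, and SPSS, the named software, fits the model.

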## 377 **15. Quality Control for the Trial**

378 We will take the following steps to perform quality control for the clinical trial:

379 We establish a dedicated research team for this trial with [name] as the

380 PI. We will establish SOP for the present study.

381 A trained staff will regularly conduct monitoring throughout the trial. The staff  
382 will examine whether the clinical facilities at the research centers meet the requirements,  
383 assure that research personnel adhere to the protocol and accurately record trial results.  
384 During each monitoring visit, the staff must also review subject data. Monitors are also  
385 responsible for ensuring that every participant in the study has signed the informed  
386 consent form.

387 The research team consists of staffs who have received GPC training and work  
388 under the guidance of senior professionals.

389 The laboratory establishes SOP and QC procedures for the experimental  
390 observation indicators.

391 Throughout the trial, the research team members hold regular weekly project  
392 coordination meetings to discuss the progress of the project and plan for the next steps.

## 393 16. The Planned Progress of the Trial

|      |                                                                                                                                                                                                                                                                                                                                                                                                                                                                                                                                                                             |
|------|-----------------------------------------------------------------------------------------------------------------------------------------------------------------------------------------------------------------------------------------------------------------------------------------------------------------------------------------------------------------------------------------------------------------------------------------------------------------------------------------------------------------------------------------------------------------------------|
| 2017 | July- September: Preparation and startup for the trial.
October- December: Collect data from 6 patients for intervention assessment and simultaneously collect data from 3 healthy controls.                                                                                                                                                                                                                                                                                                                                                               |
| 2018 | January-March: Collect data from 6 patients for intervention assessment and simultaneously collect data from 3 healthy controls.
April-June: Collect data from 6 patients for intervention assessment and simultaneously collect data from 3 healthy controls.
July- September: Collect data from 6 patients for intervention assessment and simultaneously collect data from 3 healthy controls.
October- December: Collect data from 6 patients for intervention assessment and simultaneously collect data from 3 healthy controls. |
| 2019 | January-March: Collect data from 6 patients for intervention assessment and simultaneously collect data from 3 healthy controls.
April-June: Collect data from 6 patients for intervention assessment and simultaneously collect data from 3 healthy controls.
July- September: Collect data from 6 patients for intervention assessment and simultaneously collect data from 3 healthy controls.
October- December: Collect data from 6 patients for intervention assessment and simultaneously collect data from 3 healthy controls. |

|      |                                                                                                                                                                                        |
|------|----------------------------------------------------------------------------------------------------------------------------------------------------------------------------------------|
| 2020 | 
January-March: Collect data from 6 patients for intervention assessment and simultaneously collect data from 3 healthy controls.
 
April-June: Data analysis
 |
|------|----------------------------------------------------------------------------------------------------------------------------------------------------------------------------------------|

